#### Further interventions

Participating hospitals will be encouraged to implement a protocol for early recognition of sepsis in the emergency department, recognition of deteriorating patients or patients at risk on regular wards (standardized screening for sepsis), and to establish rapid response teams, which are mandatory or widely implemented in some countries but not in Germany [70]. Furthermore, hospitals will be encouraged to get active in at least one component of the national hospital surveillance program (Krankenhaus-Infektions-Surveillance-System KISS) (http://www.nrz-hygiene.de/en/surveillance/hospital-infection-surveillance-system/).

### Study of the interventions

The effect of participating in the start-up period of the GQNS will be evaluated by comparing the participating hospitals to all other German hospitals regarding the difference between the retrospective baseline period from January 2014 to December 2015 to the intervention period from April 2016 to March 2018 (quasi-experimental difference-in-differences design) [71]. This approach is more valid than uncontrolled before-after comparisons that were used in previous quality initiatives on sepsis [23], since it is able to distinguish the intervention effect from secular changes that would have occurred without the intervention [71]. Beside secular changes, the so called Will Rogers phenomenon might bias changes in observed mortality across time [71, 72]. This phenomenon occurs if an intervention increases awareness for a disease, which results in increased detection and coding also of less severely ill cases. By incorporating an adjustment for risk factors in the difference-in-differences comparison, the analyses will try to correct for this bias. The analyses will evaluate the overall effect of participating in the GQNS, but they will not be able to distinguish which intervention elements cause possible changes.

#### Measures for studying processes and implementation of the interventions

The study coordination bureau of the GQNS receives a study report by 3M on a quarterly base that informs about the quality indicators of each participating hospital as well as about hospitals that failed to provide their claims data. Hospitals that do not provide their claims data despite several reminders are excluded from the quality collaborative. To assess fidelity and dose of the local implementation of interventions in the participating hospitals, the coordination bureau of the GQNS regularly surveys local QI team leaders by standardized online questionnaires. These questionnaires contain items regarding departments participating in the QI teams, extend of interdisciplinary analyses of quality indicators, extend of interdisciplinary case analyses, extend of education of staff, and implementation of further interventions like existence and scope of rapid response teams. The questionnaire also contains items regarding barriers to change like lacking resources or support by management, as well as items that evaluate the quality of tools and support provided by the coordination bureau. The questionnaire was developed based on results of qualitative interviews conducted during the MEDUSA trial [30]. Peer-review visits are documented and evaluated using paper-pencil surveys using standardized questionnaires both by the external peers and the involved local clinicians. These questionnaires were adapted from existing tools used in other German quality initiatives [67, 73].

#### Outcome measures

Hospital mortality of cases with sepsis with organ dysfunction (including septic shock) in the participating hospitals is the primary end-point of the study, since the newly revised consensus definitions of sepsis and septic shock (“Sepsis-3”) exclude cases without organ dysfunction [2]. Since the evaluation of the study effect relies on claims data, it is not possible to fully assess and guarantee completeness and accuracy of data. To allow hospitals to identify possible under-coding of cases with sepsis the incidence of sepsis, severe sepsis and septic shock is presented and compared between hospitals in the quality reports.

### Analyses

#### Analysis of the primary outcome

The final analysis of the intervention effect will be conducted using German national DRG data. The change in hospital mortality between the baseline period (January 2014 to December 2015) and the intervention period (April 2016 to March 2018) will be compared between the 48 hospitals initially enrolled in the GQNS and control hospitals. These are all non-participating German hospitals, whose DRG data are also available from the Federal Bureau of Statistics. Hospitals entering the GQNS after March 2016 will be excluded from this comparison. This comparison will be conducted in 2020 when the national DRG data for 2018 will be available from the Federal Bureau of Statistics. The primary analysis will evaluate the difference-in-differences in a hierarchical generalized linear model controlling for clustering of cases in hospitals by testing the statistical interaction between period (baseline vs. intervention) and group (48 hospitals enrolled in GQNS vs. control hospitals). Patient-related risk-factors will be considered as covariates. As a secondary analysis, the trajectories of change across time before and after intervention will be compared between intervention and control hospitals by a piecewise hierarchical model [74].

A preliminary evaluation of the study effect will be performed after completion of the intervention period in March 2018 but only relying on the data of the 48 intervention hospitals (before-after-comparison). A secondary preliminary analysis will be done by a piecewise hierarchical model to investigate the change in the trajectory of hospital mortality over time between periods.

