#### Sample size considerations

Concerning the baseline period (January 2014 to December 2015), 45,419 cases with sepsis were included among the initially enrolled 48 hospitals, of which 27,331 (60%) were diagnosed with sepsis with organ dysfunction (including septic shock), resulting in approximately 1000 cases per hospital across both the baseline and intervention period. Comparing the intervention hospitals with all other German hospitals across a baseline and intervention period resembles a controlled before-after trial on the cluster level. Therefore, our sample size calculation used a design factor developed for cluster-randomized before-after trials [75]. We observed a baseline mortality of 44% and an interclass correlation (ICC) of 0.02 among the included 48 hospitals. Based on the results of the Surviving Sepsis Campaign [15], a reduction in mortality to 40% was expected for the 2-year intervention period. A Fisher’s exact test comparing intervention and control conducted at α-level 0.05 with a power of 0.9 would require a total sample size of 6476. Correcting this sample size by the obtained design factor of 3.75, a total of 26 hospitals (13 control and 13 intervention) each including 1000 cases would be necessary in a cluster randomized before-after trial. Given 48 intervention hospitals and more than 1000 control hospitals in the national German DRG data, our study should be adequately powered to detect the expected intervention effect.

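### The primary difference-in-differences model names only clustering of cases in hospitals; fitted with a hospital intercept alone, its period-by-group test is too liberal if hospitals change differently between periods

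*Protocol article*

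**What the plan says.** The section on analysis of the primary outcome specifies that the difference-in-differences will be evaluated "in a hierarchical generalized linear model controlling for clustering of cases in hospitals by testing the statistical interaction between period" and "group (48 hospitals enrolled in GQNS vs. control hospitals"), with patient-related risk factors as covariates. It describes the random-effects structure no further: it neither says that a hospital intercept is the only random effect nor mentions a random period effect, a hospital-by-period level or robust standard errors.

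The sample size section treats the design as a before-after comparison at hospital level. It gives "We observed a baseline mortality of 44% and an interclass correlation (ICC) of 0.02 among the included 48 hospitals", and the expectation that "a reduction in mortality to 40% was expected for the 2-year intervention period". The unadjusted requirement is stated as "A Fisher’s exact test comparing intervention and control conducted at α-level 0.05 with a power of 0.9 would require a total sample size of 6476". It continues: "Correcting this sample size by the obtained design factor of 3.75, a total of 26 hospitals (13 control and 13 intervention"), each with 1000 cases. The article gives neither the formula behind 3.75 nor the correlation of a hospital's rates between the two periods.

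**The concern.** The period-by-group interaction is a within-hospital contrast: each hospital is compared with itself, and the changes are then compared between groups. A random hospital intercept describes stable differences between hospitals, and these largely drop out of that contrast. What is left is binomial sampling error plus the extent to which hospitals change differently from one another. A shift common to all hospitals is absorbed by the period term; hospital-specific drift is not. A binomial model has no free residual variance to pick it up.

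The article itself gives reasons to expect such drift. Its interventions section makes only reporting and publication mandatory and leaves hospitals to choose the rest. Its sensitivity-analysis section anticipates coding changes and separates hospitals with high and low improvement effort. If drift is present and the model has no term for it, ordinary differences between hospitals in how they change can be read as an effect of the network, with confidence intervals that are too narrow.

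**Working it through.** **Inputs from the article (sample size section).** Mortality p = 0.44, so p(1-p) = 0.2464; ICC = 0.02; 48 intervention hospitals; more than 1000 controls (1000 used here). Cases per hospital-period: 27,331/48 = 569 in the baseline period. The article's own rounding, about 1000 over both periods, gives 500.

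**Assumptions.** The cluster autocorrelation (CAC), the correlation of a hospital's true rates between the two periods, is not in the article, so a range of 0.80 to 1.00 is shown. Also assumed: 569 cases in the intervention period too, equal hospital sizes and no covariate adjustment.

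**Step 1: the plan's own figures.** For 44% vs 40%, two-sided 5%, power 90%:

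- n per group = [1.96·√(2·0.42·0.58) + 1.2816·√(0.2464 + 0.24)]² / 0.04² = 3198, total 6396; with continuity correction 2 × 3248 = 6496. The stated 6476 lies between these.
- 6476 × 3.75 = 24,285, or 24.3 hospitals of 1000 cases, which becomes 26 when rounded up to equal groups.

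The sample size reproduces.

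**Step 2: what 3.75 implies.** With 500 cases per period the ordinary design effect is 1 + 499 × 0.02 = 10.98. At CAC = 1 the correlation of observed hospital rates is r = 500 × 0.02/10.98 = 0.911. The covariance-analysis factor is 10.98 × (1 - r²) = 1.873. Doubled for two measurement periods, it is 3.745, which matches 3.75.

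The same value can be reached without doubling at a lower CAC:

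- about 0.89 (covariance analysis) or 0.91 (change scores) with 500 cases per period;
- about 0.91 or 0.92 with 569;
- about 0.95 or 0.96 with 1000.

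**Step 3: size of the test with a hospital intercept only.** Per hospital-period:

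- binomial part e = p(1-p)(1 - ICC)/m = 0.2464 × 0.98/569 = 0.000424;
- drift part h = p(1-p) × ICC × (1 - CAC) = 0.004928 × (1 - CAC);
- variance ratio R = (e + h)/e;
- true type I error = 2[1 - Φ(1.96/√R)];
- model SE = √[2e(1/48 + 1/1000)] = 0.43 percentage points; true SE = model SE × √R;
- SD of a hospital's true change = √(2h).

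| CAC (assumed) | R | Type I error | True SE (points) | SD of a hospital's true change (points) |
|---|---|---|---|---|
| 1.00 | 1.00 | 5.0% | 0.43 | 0 |
| 0.99 | 1.12 | 6.4% | 0.46 | 1.0 |
| 0.95 | 1.58 | 11.9% | 0.54 | 2.2 |
| 0.90 | 2.16 | 18.2% | 0.63 | 3.1 |
| 0.80 | 3.32 | 28.2% | 0.78 | 4.4 |

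With 500 cases per hospital-period the type I errors at 0.99, 0.95, 0.90 and 0.80 are 6.2%, 11.1%, 16.8% and 26.1%.

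**Step 4: simulation check.** With 48 and 1000 hospitals, and control hospitals of 200 or 569 cases per period, the test that ignores drift rejected in 5.4%, 10.5-11.9%, 17-18% and 27-29% of null runs at CAC 1.00, 0.95, 0.90 and 0.80. A test based on hospital-level changes, which allows for drift, stayed at 4.3-5.7% throughout.

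**The case against.** The strongest objection is that the article never says that a hospital intercept is the only random effect. A hierarchical model for cases in hospitals can carry a random period slope, and a condensed article may leave that to an analysis plan that is not shown. This stands: a reader might infer that the plan ignores hospital-by-period variation, but the text only fails to name it. The point is still more than missing detail. The article does state the dependence to be controlled, and following that sentence in its ordinary two-level form gives the wrong variance for the contrast being tested.

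Second, the autocorrelation is unknown. A reader might conclude that the type I error is well above 5%. The documents do not support that as an unconditional statement: at 1.00 there is no inflation and at 0.99 it is small.

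Third, patient risk factors are covariates in the primary model, and coding changes have their own planned comparison. Drift due to measured case-mix may therefore be partly removed, whereas the calculation above is unadjusted. This stands as a reason to treat the figures as indicative; adjustment cannot be assumed to remove all hospital-specific change.

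Fourth, a reader might take 3.75 as proof that planning assumed perfectly stable hospital rates. The match at autocorrelation 1 is close and needs no free parameter, but Step 2 shows that the undoubled formulas reach the same value at about 0.89-0.96. The cited formula is not shown, so the factor is supportive at most. On that second reading, planning would have allowed for drift that the primary model does not name.

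**Conclusion.** The concern holds conditionally. If the primary model is fitted with a hospital intercept only, and hospitals do not all change alike between periods, the period-by-group test is anti-conservative: about 6%, 12%, 18% and 28% at autocorrelation 0.99, 0.95, 0.90 and 0.80, against a nominal 5%. These figures rest on the article's ICC, mortality and baseline case count. They also assume an autocorrelation range, equal hospital sizes and no gain from covariates. Neither the intercept-only fit nor the autocorrelation is stated in the article, so this is a choice left open in a way that invites the wrong standard error, not a demonstrated error in the result. Because the confirmatory test of a non-randomised study depends on it, the structure should be fixed explicitly.

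**What to change.** State in the analysis of the primary outcome that the model includes a random hospital-by-period effect, that is, a random intercept and a random period slope for each hospital. Alternatively, state that the period-by-group interaction is tested with hospital-level cluster-robust standard errors.

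The cost is one sentence and wider confidence intervals where drift exists: at autocorrelation 0.95 to 0.80 the standard error goes from about 0.43 to 0.54-0.78 percentage points, an increase of 26% to 82% (√1.58 = 1.26; √3.32 = 1.82). Power for the expected 4-point reduction stays above 99% even at 0.80. If hospital rates prove fully stable, almost nothing is lost. If an analysis plan already specifies one of these approaches, the article's wording only needs to be aligned with it.

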#### Sensitivity analyses and planned subgroup analyses

Differences across time between hospitals of the GQNS and control hospitals might result from changes in coding in the intervention hospitals, e.g., improved ICD-coding of sepsis or comorbidities. Therefore, incidences of sepsis without organ dysfunction, sepsis with organ dysfunction and septic shock as well as incidences of mortality risk-factors will be compared across time between intervention and control hospitals. Analyses of the primary outcome will be repeated within these three subgroups of sepsis cases.

Additionally, hospitals will be categorized based on the degree of their QI efforts during the intervention period but without inspection of their primary outcome. The categorization will be based on the results of the regularly conducted surveys of local QI team leaders. The analyses of the primary end-point will be repeated within the subgroups of hospitals with high QI effort and hospitals with low QI effort.

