## Appendix

### Definition of cases with sepsis by German ICD-10 codes

Sepsis without organ dysfunction: A40.0, A40.1, A40.2, A40.3, A40.8, A40.9, A41.0, A41.1, A41.2, A41.3, A41.4, A415.1, A41.52, A41.58, A41.8, A41.9, R65.0.

Sepsis with organ dysfunction but without septic shock: R65.1.

Septic shock: R57.2.

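### The primary denominator is a coded severity class that the programme could shift, and no planned effect estimate is unaffected by movement between classes

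*Protocol article*

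**What the plan says.** Under Outcome measures: "Hospital mortality of cases with sepsis with organ dysfunction (including septic shock) in the participating hospitals is the primary end-point of the study". The Appendix defines the classes by ICD-10 code alone, for example "Sepsis with organ dysfunction but without septic shock: R65.1", with R57.2 for septic shock.

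Several parts of the programme bear on coding or recognition. The quality reports show incidence for a stated purpose: "To allow hospitals to identify possible under-coding of cases with sepsis the incidence of sepsis, severe sepsis and septic shock is presented". The Case analyses section has hospitals review low-risk deaths for problems of care or of ICD-10 coding. Staff education aims at awareness and early recognition.

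The plan knows the threat. Study of the interventions describes the Will Rogers phenomenon and answers it with covariates: "By incorporating an adjustment for risk factors in the difference-in-differences comparison, the analyses will try to correct for this bias". The section on sensitivity and subgroup analyses names changed coding of sepsis or comorbidities in the intervention hospitals as a possible explanation of a difference. It plans to compare incidences of the three classes and of risk factors over time between the groups. It then adds: "Analyses of the primary outcome will be repeated within these three subgroups of sepsis cases". The article describes no effect estimate over all coded sepsis cases together.

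**The concern.** Difference-in-differences removes changes common to both groups. Coding feedback and training delivered through the network reach the participating hospitals and not the controls, so a coding change that they cause would stay in the interaction term.

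The within-class repetition looks like a check on this, but each of its denominators is defined by the codes in question. A case recoded from sepsis without organ dysfunction to R65.1 may be sicker than the average of the class it leaves and less sick than the average of the class it enters. Its move then lowers mortality in both. Results that agree across classes could be read as confirming a benefit when only labels have changed. At stake is part of a planned effect of four percentage points.

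**Working it through.** **Inputs from the protocol article (Sample size considerations).** All coded sepsis at baseline in the 48 hospitals: 45,419. With organ dysfunction, including shock: 27,331. Baseline mortality in that class: 44%; expected: 40%.

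**Plan's own figures.**
- Share with organ dysfunction: 27,331 / 45,419 = 60.2%, against the stated 60%. The rest, 45,419 − 27,331 = 18,088, is sepsis without organ dysfunction.
- Total sample size for 44% against 40%, two-sided 0.05, power 0.9: the normal approximation gives 2 × 3,198 = 6,396, or 2 × 3,248 = 6,496 with continuity correction. The stated 6,476 for Fisher's exact test lies between them. No stated figure is wrong on this point.

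**Assumptions.** The article gives neither mortality without organ dysfunction nor mortality of cases that might be recoded. The values below are assumed and varied. All results are crude, whereas the planned model is adjusted.

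**1. Movement between classes, no true effect.** Lower class at 12%; 3,000 cases with 20% mortality (600 deaths) recoded upward.
- Lower class: (18,088 × 0.12 − 600) / 15,088 = 1,570.6 / 15,088 = 10.4%, from 12.0%.
- Primary class: (27,331 × 0.44 + 600) / 30,331 = 12,625.6 / 30,331 = 41.6%, from 44.0%.
- All coded sepsis: (2,170.6 + 12,025.6) / 45,419 = 31.3%, before and after.

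**2. Other assumed values.** Lower class at 15%; 15% of it (2,713 cases) recoded, with 22% mortality (597 deaths).
- Lower class: (2,713 − 597) / 15,375 = 13.8%, from 15.0%.
- Primary class: (12,026 + 597) / 30,044 = 42.0%, from 44.0%.
- Pooled: unchanged.

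**3. When the repetition would show it.** Lower class at 20%; 4,373 cases with 15% mortality leave. Lower class: (3,617.6 − 656.0) / 13,715 = 21.6%, a rise. The masking needs recoded cases whose mortality lies between the class means.

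**4. Size of shift that imitates the whole effect.** With recoded mortality p, the number needed is m = 27,331 × (0.44 − 0.40) / (0.40 − p).
- p = 0.15: m = 4,373, which is 24% of the lower class; the share with organ dysfunction rises from 60% to 70%.
- p = 0.25: m = 7,288, which is 40% of the lower class; the share rises to 76%.

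**5. Would the incidence comparison see it?** Moving 1,000 cases takes the share from 60.2% to 62.4%. With 45,419 cases per period and the plan's design factor of 3.75 borrowed as a variance inflation (illustration only), z is about 3.5. For 500 cases z is about 1.75.

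**6. Limit of pooling.** Suppose 10% extra primary-class cases (2,733) with 20% mortality (546.6 deaths) come from outside all sepsis codes.
- Primary class: (12,025.6 + 546.6) / 30,064 = 41.8%.
- Pooled, with the lower class at 12%: (14,196.2 + 546.6) / 48,152 = 30.6%, from 31.3%.

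Pooling does not remove this form of the bias. Deaths with a sepsis code per inpatient case would rise by 546.6 deaths over an unchanged denominator; extra coding cannot lower that rate.

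**The case against.** The strongest reply is that the plan already meets the problem. It names the phenomenon, adjusts for patient risk factors, and compares incidences of classes and risk factors between groups. Step 5 shows that a shift large enough to matter greatly would probably be seen. The article also does not say outright that the within-class repetition is the coding check; the incidence comparison is what it ties directly to that worry. Movement from the lower class into R65.1 leaves the septic shock subgroup untouched, so that subgroup stays informative unless there is also movement into shock. The direction is open as well: earlier treatment may keep good responders out of the organ-dysfunction class, which would raise coded-class mortality and hide a benefit. Finally, an unseen analysis plan might contain further analyses.

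Much of this stands, and it rules out stronger readings that a reader might infer. The documents do not show that the programme does shift the class; they call a coding change possible. They do not support saying that the repetition can never reveal migration (step 3), or that a spurious effect of the full four points would pass unnoticed (steps 4 and 5).

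The gap remains. An incidence comparison detects a net shift but yields no corrected effect estimate, and flows in opposite directions can cancel in it. The covariates come from the same claims data, and the plan itself concedes that comorbidity coding may change. The point concerns a safeguard that the article does fix, not detail left to another document.

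**Conclusion.** The concern holds as a possible differential bias that the stated analyses do not resolve. The primary denominator is set by codes on which the programme gives feedback, and none of the effect estimates described is unaffected by movement between classes. Within-class repetition gives false reassurance when recoded cases have intermediate mortality. Under the assumed values in steps 1 and 2, recoding of 15% to 17% of the lower class produces a crude fall of 2.0 to 2.4 points in the primary class with no death avoided, about half the planned effect or slightly more.

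These sizes rest on assumed class mortalities and ignore risk adjustment, which would remove an unknown part. Shifts of that size would probably appear in the incidence comparison. The realistic risk is therefore a primary estimate known to be contaminated, with no planned analysis to show how much of it remains.

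**What to change.** In the section on sensitivity and subgroup analyses:

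1. Add, as a named sensitivity analysis, the same adjusted difference-in-differences model in all coded sepsis cases pooled (every Appendix code). Leave the class codes out of the covariates, so that movement between classes cannot affect the result.
2. Because pooling does not protect against cases newly coded from outside these codes, also report coded sepsis deaths per all inpatient cases of the hospital, with the same group-by-period contrast. The article describes the DRG data set as covering all treated cases. Extra sepsis coding cannot lower this rate, so it is a conservative complement.
3. State that the primary result will be interpreted together with these two analyses and the incidence comparison. A strict rule that all must point the same way is not advisable, since each has its own weakness.
4. State that the within-class repetition is a subgroup description and not evidence against coding drift.

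The cost is two further model runs on the same DRG data. The pooled estimate is diluted by lower-mortality cases and remains open to drift in comorbidity coding through the covariates. Deaths per inpatient case can rise when deaths are newly coded as sepsis, which may mask a real benefit. Both limits should be stated with the results.

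### The QI-effort analysis reduces survey information on degree of effort to high and low in 48 hospitals and never estimates how the mortality change varies with effort; a slope term on the same data would.

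*Protocol article*

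**What the plan says.** The section on sensitivity and subgroup analyses states that "hospitals will be categorized based on the degree of their QI efforts during the intervention period", and that this is done without looking at the primary outcome. On the source it says: "The categorization will be based on the results of the regularly conducted surveys of local QI team leaders". On the analysis it says: "The analyses of the primary end-point will be repeated within the subgroups of hospitals with high QI effort and hospitals with low QI effort".

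The section on measures for processes and implementation gives the purpose of those surveys: "To assess fidelity and dose of the local implementation of interventions in the participating hospitals". Among the items it lists "extend of interdisciplinary analyses of quality indicators, extend of interdisciplinary case analyses, extend of education of staff", and further interventions such as the existence and scope of rapid response teams. It gives no response scale, summary score, distribution or cut-point.

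The primary analysis tests period by group, with the groups given as "48 hospitals enrolled in GQNS vs. control hospitals". The Interventions section makes only the reporting, benchmarking and publication of indicators mandatory, so effort on the other elements can differ between hospitals.

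**The concern.** The survey is meant to capture dose, and several items ask how far an activity went. The analysis keeps two classes. Hospitals just either side of the cut are treated as opposites, and differences within a class are ignored.

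The stated analysis also does not relate effort to outcome directly. It gives two separate estimates, high-effort hospitals against controls and low-effort hospitals against controls, with no contrast between them and no trend. A reader who wants to know whether more effort went with a larger fall in mortality must compare the two by eye.

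Effort varies only between 48 hospitals, so the information is scarce. The Discussion allows that two years may be too short for a substantial overall effect. In that case a gradient with effort would be among the more useful remaining evidence, and the plan has no estimate of it.

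**Working it through.** **Inputs.** From the sample size section: 48 intervention hospitals; 27,331 baseline cases with organ dysfunction, so 27,331/48 = 569 per hospital and period; baseline mortality 44%; ICC 0.02; expected mortality 40%. Assumed, because the article does not give them: the shape of the score, the cut-point, a linear relation with the change in mortality, and the correlation c between a hospital's true mortality in the two periods.

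**1. The plan's own figure.** For 44% against 40%, two-sided 0.05 and power 0.9, the normal approximation gives 6396 cases in total, or 6496 with continuity correction; the stated 6476 is reproduced to within about 1.3%. Taking the design factor of 3.75 as given, 6476 × 3.75 = 24,285 cases, or 12.1 hospitals of 1000 cases per arm, rounded up to 13 + 13. This concerns the overall comparison. No figure is stated for the effort analysis.

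**2. Information kept by a split.** This is the squared correlation between the score and its high/low version. For a normal score with share p in one class it is φ(z_p)²/[p(1−p)]; for a uniform score it is 3p(1−p).

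| Score and split | Kept | Lost |
|---|---|---|
| Normal, 50/50 | 64% | 36% |
| Normal, 33/67 | 59% | 41% |
| Normal, 25/75 | 54% | 46% |
| Normal, 20/80 | 49% | 51% |
| Uniform or bimodal, 50/50 | 75% | 25% |
| Beta(2,2), 50/50 | 70% | 30% |
| 3 to 7 evenly used levels, best split | 75–80% | 20–25% |
| Exponential skew, 50/50 | 48% | 52% |

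A normal score split at the median makes 48 hospitals count like 48 × 0.637 = 31. The detectable effect grows by 1/√(kept): about 25% for that case (1/√0.637 = 1.253), from 12% (kept 0.80) to 44% (kept 0.48) across the table.

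**3. Correlation scale.** Fisher's z with SE 1/√45, two-sided 0.05. The smallest correlation detectable with 80% power is tanh(2.80/√45) = 0.39 with the score. With a median split of a normal score, the true correlation must be 0.39/√0.637 = 0.49. At a true correlation of 0.40, power is 81% with the score, 60% with a median split and 53% with a 25/75 split.

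**4. Mortality scale, for a high-low contrast (not a stated analysis).** SD of a hospital's change = √{2[0.02 × 0.2464 × (1−c) + 0.2464/569]}, with 0.2464 = 0.44 × 0.56. Detectable differences are at 80% power, in percentage points.

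| c | SD of change | SE, 24 v 24 | Split (× 2.80) | Normal score (÷ 1.253) |
|---|---|---|---|---|
| 1.0 | 2.94 | 0.85 | 2.4 | 1.9 |
| 0.9 | 4.30 | 1.24 | 3.5 | 2.8 |
| 0.8 | 5.33 | 1.54 | 4.3 | 3.4 |

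The whole network effect is planned at 44 − 40 = 4 points.

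**5. The stated analysis.** For 24 hospitals against a very large control group, the SE is about SD/√24 = 0.60/0.88/1.09, and the detectable effect is about 1.7/2.5/3.0 points before the small addition from control variance.

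**The case against.** The best reply is that the plan does not test high against low. It asks whether each class improved relative to controls. Step 5 shows that with an even split this question can be answered for effects below the planned 4 points, and the sample size section asks for only 13 intervention hospitals. That stands: the losses in steps 2 to 4 belong to a contrast the article does not state. It does not remove the gap, because with no contrast and no trend nothing estimates the relation with effort.

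Second, no score exists in the article. The items are mixed, and few-level scores split near the middle lose only 20–30%. That stands too. A reader might infer that a third or more of the information is certainly lost; this requires a near-normal or skewed score or an uneven cut, and the article fixes none of these.

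Third, a reader might infer that using the score costs nothing. It needs no new data, but unlike items must be combined in advance and a trend assumed. If effort acts through a threshold, the advantage can shrink or reverse. Sorting hospitals into high and low also needs a summary of effort, so much of the building work is required either way.

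Fourth, scoring details may lie in an analysis plan that is not shown. The missing cut-point is therefore no criticism. The two-class rule itself is stated.

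Finally, an effort slope might be expected to show which elements work. It would not: the section on the study of the interventions says the analyses cannot separate elements, and a single score does not change that.

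**Conclusion.** The point holds as an improvement to a supportive analysis. As stated, the plan keeps two effort classes and estimates no relation between effort and mortality change. If that relation is roughly linear, a high-low comparison would lose about 20% to 50% of the information in a graded score, 36% for a normal score split at the median. Under the linear model, the score detected a smaller effect than the split in every shape examined.

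The range rests on assumed score shapes and cut-points. The figures in points also rest on the assumed correlation between periods. A reader might go further and call the stated subgroup analyses underpowered or the primary result compromised. The documents support neither: the subgroup comparisons with controls are reasonably sized under an even split, and the primary period-by-group test does not use the effort classes.

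**What to change.** Before the primary outcome is inspected, fix one summary effort score from the existing questionnaires: which items and survey rounds enter, and with what weights.

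In the difference-in-differences model, keep group, period and group × period. Add the effort score as a main effect and effort score × period. Centre and standardize the score within the 48 hospitals and set it to zero for controls, which have no survey. The slope is then estimated from the 48 hospitals only, and the group × period term is the network effect at average effort. A score-by-period term without the group-by-period term would be wrong, because zero would place controls at average network effort.

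Report the change in mortality per SD of effort with its confidence interval. Keep the results for "hospitals with high QI effort and hospitals with low QI effort" as description and as a check on the assumed trend; a rank score is an alternative if the distribution is awkward.

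Cost: a few lines of analysis text and the advance work on the score. No new data are needed, and the primary analysis is unchanged.
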